## Abstract

**Background:**

Patients with high-risk prostate cancer are at increased risk of lymph node metastasis and are thought to benefit from whole pelvis radiotherapy (WPRT). There has been recent interest in the use of hypofractionated radiotherapy in treating prostate cancer. However, toxicity and cancer outcomes associated with hypofractionated WPRT are unclear at this time. This phase II study aims to investigate the impact in quality of life associated with hypofractionated WPRT compared to conventionally fractionated WPRT.

**Methods:**

Fifty-eight patients with unfavourable intermediate-, high- or very high-risk prostate cancer will be randomized in a 1:1 ratio between high-dose-rate brachytherapy (HDR-BT) + conventionally fractionated (45 Gy in 25 fractions) WPRT vs. HDR-BT + hypofractionated (25 Gy in 5 fractions) WPRT. Randomization will be performed with a permuted block design without stratification. The primary endpoint is late bowel toxicity and the secondary endpoints include acute and late urinary and sexual toxicity, acute bowel toxicity, biochemical failure-, androgen deprivation therapy-, metastasis- and prostate cancer-free survival of the hypofractionated arm compared to the conventionally fractionated arm.

**Discussion:**

To our knowledge, this is the first study to compare hypofractionated WPRT to conventionally fractionated WPRT with HDR-BT boost. Hypofractionated WPRT is a more attractive and convenient treatment approach, and may become the new standard of care if demonstrated to be well-tolerated and effective.

**Trial registration:**

This trial was prospectively registered in ClinicalTrials.gov as NCT04197141 on December 12, 2019.

## Background

Patients with high-risk prostate cancer are at increased risk of lymph node metastasis [1]. Whole pelvis radiotherapy (WPRT) is posited to be beneficial in this population by eradicating microscopic disease outside the prostate. However, two randomized trials failed to demonstrate meaningful oncological improvements with WPRT compared to radiation to the prostate alone [2, 3]. Potential caveats may explain the lack of benefit in these trials, including use of lower doses of radiation (between 66 and 70 Gy in conventional fractionation [1.8–2 Gy per fraction]) to the prostate, which may have resulted in local progression and a second wave of metastasis; inclusion of patients at low risk of nodal disease (< 15%) thereby reducing the potential benefit of elective irradiation; and small pelvic fields without coverage of the common iliac chains.

More recently, Radiation Therapy Oncology Group (RTOG) 0924 completed accrual and is expected to definitively evaluate the role of conventionally fractionated WPRT in intermediate- and high-risk disease. However, there is already evidence that has indirectly supported the use of WPRT in high-risk prostate cancer patients. In the ASCENDE-RT trial, a WPRT + low-dose-rate brachytherapy boost strategy led to encouraging results, with 83% biochemical failure-free survival at 9 years in a cohort comprising of approximately 70% high-risk patients [4]. A recently published multicentre prospective cohort study also supports the use of WPRT in higher-risk patients, demonstrating significantly improved 5-year biochemical failure-free survival rates (84% vs. 77%, *p* = 0.001) for high-risk prostate cancer patients who received WPRT + high-dose-rate brachytherapy (HDR-BT) compared to prostate-only radiotherapy + HDR-BT [5]. Furthermore, WPRT was the superior arm in the recently presented RTOG 0534 trial [6]. In this study of patients who had biochemical failure after prostatectomy, the authors identified a 7% increase in freedom from progression in the WPRT arm compared to the prostate bed radiotherapy arm. Arguably, this benefit could be extrapolated to a cohort of high-risk patients naïve to treatment. Several retrospective series have also suggested the benefit of WPRT in prostate cancer patients [7, 8].

In parallel to studies evaluating the role of WPRT in prostate cancer, radiotherapy technique has improved in the last few decades. Technological advances, such as intensity-modulated radiotherapy (IMRT), volumetric-modulated arc therapy (VMAT) and image-guided radiotherapy, have allowed radiation oncologists to more accurately target volumes while sparing more normal tissue. In conjunction with the favourable tumour radiobiology (i.e. a low alpha/beta ratio) of prostate cancer cells, researchers have investigated the role of hypofractionated treatments (> 2 Gy per fraction) in patients with prostate cancer. A recent randomized control trial involving multiple centres showed no difference in late toxicity and cancer control between ultra-hypofractionated (≥ 5 Gy per fraction) and conventionally fractionated radiotherapy to the prostate alone [9].

The use of ultra-hypofractionation in WPRT is still in its infancy and the toxicity associated with this strategy is unclear. To our knowledge, only two small, single-arm studies have reported outcomes associated with this treatment. In both of them, a simultaneous boost was delivered to the prostate and proximal seminal vesicles. In the SATURN study [10], authors reported an acceptable toxicity profile with this approach, while authors from the FASTR trial had higher than anticipated late toxicities resulting in early trial discontinuation [11].

Currently, clinical trials such as the French SHORT trial (NCT03417336) randomize higher-risk prostate cancer patients between HDR-BT + WPRT (25 Gy in 5 fractions) versus stereotactic radiotherapy to the prostate + WPRT. However, there is no current data comparing the toxicity profile between conventionally fractionated WPRT (45 Gy in 25 fractions) versus hypofractionated WPRT (25 Gy in 5 fractions), and long-term bowel toxicity associated with this approach is unknown. Moreover, the genitourinary safety profile associated with hypofractionated WPRT plus HDR-BT boost has not yet been fully investigated.

This study aims to investigate the impact in quality of life associated with hypofractionated WPRT compared to conventionally fractionated WPRT. This information is valuable as hypofractionated WPRT is a more attractive and convenient treatment approach, and may become the new standard of care if demonstrated to be well-tolerated and effective. We hypothesize that hypofractionated WPRT is non-inferior with respect to quality of life outcomes compared to conventionally fractionated WPRT. Therefore, this study aims to provide a more rational justification for use of hypofractionated WPRT in future larger randomized trials by comparing this strategy with the current standard of care. This study will also provide an initial understanding of the toxicity profile and cancer control associated with hypofractionated WPRT and HDR-BT.

## Methods/Design

### Objectives

Determine if hypofractionated WPRT is non-inferior to conventionally fractionated WPRT with respect to bowel function and quality of life in prostate cancer patients treated with HDR-BT boost.Assess safety, efficacy and quality of life outcomes between both treatment strategies.

### Study design

This is a phase II, open label trial, randomizing 58 unfavourable intermediate-, high- or very high-risk prostate cancer patients between HDR-BT + conventionally fractionated (45 Gy in 25 fractions) WPRT (Arm 1: 29 patients) vs. HDR-BT + hypofractionated (25 Gy in 5 fractions) WPRT (Arm 2: 29 patients) (Fig. 1).

**Fig. 1 Fig1:**
[figure not shown]
Study schema. Abbreviations: NCCN – National Comprehensive Cancer Network; MSKCC – Memorial Sloan Kettering Cancer Center

The study will employ a 1:1 randomization between Arm 1 and Arm 2 in a permuted block design without stratification with the size of the blocks known only to the statistician.

### Endpoints

#### Primary endpoint

Late bowel toxicity and quality of life measured using the Expanded Prostate Cancer Index Composite (EPIC) bowel function subdomain at 1 year post-treatment

#### Secondary endpoints

Acute urinary and sexual toxicity and quality of life measured using the EPIC urinary and sexual domains at 6 weeks post-treatmentAcute bowel toxicity and quality of life measured using the EPIC bowel domain at 6 weeks post-treatmentLate urinary and sexual toxicity quality of life measured using the EPIC urinary and sexual domains at 1 year post-treatmentLate bowel toxicity quality of life measured using the EPIC bowel bother subdomain at 1 year post-treatmentInternational Prostate Symptom Score (IPSS), Patient-Oriented Prostate Utility Scale (PORPUS-U) and EuroQOL 5-Dimension 5-Level (EQ-5D-5L) measured at 6 weeks, 1 year and 2 years post-treatmentUrinary, bowel and sexual toxicity measured by the Common Terminology Criteria for Adverse Events (CTCAE) version 5.0 measured at 6 weeks, 1 year and 2 years post-treatmentProstate-specific antigen (PSA) response rate at 4 years post-treatmentCost effectiveness analysis of the hypofractionated arm compared to the conventionally fractionated armFreedom from local failure: Time from randomization to first local failure, or last follow-up, whichever occurs first.Freedom from regional failure: Time from randomization to first regional failure, or last follow-up, whichever occurs first.Biochemical failure-free survival: Time from randomization to biochemical failure (based on the Phoenix definition), death from any cause, or last follow-up, whichever occurs first.Androgen deprivation therapy (ADT)-free survival: Time from randomization to start of salvage ADT, death from any cause, or last follow-up, whichever occurs first.Metastasis-free survival: Time from randomization to development of metastasis, death from any cause, or last follow-up, whichever occurs first.Prostate cancer-free survival: Time from randomization to death attributed to prostate cancer, or last follow-up, whichever occurs first.Overall survival: Time from randomization to death from any cause, or last follow-up, whichever occurs first.

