### Follow-up evaluation and assessment of efficacy

The follow-up schedule is shown in Table 2. Day 1 of follow-up will correspond with the last day of WPRT. Additional imaging or laboratory investigations should be carried out at the discretion of the oncologist, based on findings in the history or physical examination. Additional treatment (e.g. salvage treatment with surgery or further radiotherapy) is at the discretion of the treating physicians, and will be captured in the case report form.

**Table 2 Tab2:** Study follow-up schedule

	Baseline^a^	First day of WPRT	Last day of WPRT	6 weeks post-WPRT	Follow up (months)^b^						
					6	12	18	24	36	48	60
Physical Examination	X			X	X	X	X	X	X	X	X
Imaging	X										
PSA	X				X	X	X	X	X	X	X
EPIC	X	X	X	X	X	X	X	X	X	X	X
IPSS	X	X	X	X	X	X	X	X	X	X	X
CTCAE	X	X	X	X	X	X	X	X	X	X	X
Survival and disease status					X	X	X	X	X	X	X
EQ-5D and PORPUS-U	x			x		x		x			

*Abbreviations*: *WPRT* whole pelvis radiotherapy, *PSA* prostate specific antigen, *EPIC* Expanded Prostate Cancer Index Composite, *IPSS* International Prostate Symptom Score, *CTCAE* Common Terminology Criteria for Adverse Events, *EQ-5D-5L* EuroQOL 5-Dimension 5-Level, *PORPUS-U* Patient-Oriented Prostate Utility Scale

^a^Baseline assessments to be completed prior to high-dose-rate brachytherapy

^b^Follow-up schedule determined based on day of last WPRT treatment

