#### Analysis plan

Patients will be analyzed in the groups to which they are assigned (intention-to-treat).

Comparisons between treatment arms for acute and late urinary, bowel and sexual quality of life end points will be performed using the two-sample t-test for non-inferiority. Quality of life data is anticipated to be normally distributed. In the event such data is not normally distributed, the Wilcoxon rank sum test for non-inferiority will be substituted as appropriate. Similarly, IPSS data is anticipated to be normally distributed and will follow similar methodology. Differences in urinary, bowel and sexual toxicity and PSA response rate at 4 years post-treatment between treatment arms will be compared using the Chi–square test or Fisher’s exact test as appropriate. Time-to-event end points (e.g. overall survival) will be compared between treatment arms using Kaplan-Meier estimates and the log-rank test.

In the event the non-inferiority criteria is met for the primary end point (late bowel function quality of life based on EPIC), a secondary analysis to investigate superiority of the experimental arm will take place. This will be performed using the two-sample t-test (or Wilcoxon rank sum test as appropriate as similarly discussed above). A 5-point difference in scores will be considered a clinically meaningful change.

For each quality of life domain and IPSS data, linear mixed effects models will be generated to test for differences between treatment arms over time. Cox proportional hazards univariable and multivariable regression models will be used to identify baseline factors predictive of time-to-event end points (e.g. overall survival).

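### Biochemical failure-free survival counts only Phoenix failure or death, so a man given discretionary salvage before Phoenix failure is carried as failure-free until a later event

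*Protocol article*

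**What the plan says.** Under Secondary endpoints, the Protocol article gives the event list for this endpoint: "Biochemical failure-free survival: Time from randomization to biochemical failure (based on the Phoenix definition), death from any cause, or last follow-up, whichever occurs first". A neighbouring endpoint, ADT-free survival, does treat one form of salvage as an event: "Time from randomization to start of salvage ADT, death from any cause, or last follow-up, whichever occurs first". Metastasis-free survival counts metastasis or death, and freedom from local failure and freedom from regional failure are defined separately. None of these names salvage surgery or salvage radiotherapy as an event.

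Under Follow-up evaluation and assessment of efficacy, the article states: "Additional treatment (e.g. salvage treatment with surgery or further radiotherapy) is at the discretion of the treating physicians". The same sentence says this treatment is recorded in the case report form. No PSA level that would prompt salvage is given. Table 2 schedules PSA at 6, 12, 18, 24, 36, 48 and 60 months and schedules no imaging after baseline. Further tests are at the oncologist's discretion.

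The Study design section describes the trial as open label: "This is a phase II, open label trial, randomizing 58 unfavourable intermediate-, high- or very high-risk prostate cancer patients". The Analysis plan then says: "Time-to-event end points (e.g. overall survival) will be compared between treatment arms using Kaplan-Meier estimates and the log-rank test".

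**The concern.** Salvage is given because the disease is thought to have returned. If it starts while the PSA is still short of Phoenix failure and it lowers the PSA, the listed event may come late or not at all within follow-up. Under the definition as written, the man stays in the failure-free group in the meantime, although his disease has needed further treatment. The endpoint then depends partly on how quickly physicians act and not only on how often the cancer returns.

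Two consequences need to be kept apart. The first needs no difference between arms: early salvage in both arms raises the reported failure-free rate in both. The second needs a difference in timing. The physician who decides on salvage knows the allocation, so timing could differ by arm, and the comparison would then move for a reason unrelated to tumour control.

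The Background section says the trial is to give an initial understanding of cancer control to support larger trials. The failure-free rate is therefore likely to be read and carried forward even though the trial is not sized for it.

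**Working it through.** **Design figure in the plan.** The only sample size calculation is for the primary endpoint (EPIC bowel function, margin 5 points, SD 5, alpha 0.05, power 0.90). The normal approximation with a two-sided alpha gives 2 × (1.960 + 1.282)² × 5²/5² = 21.0, rounded up to 22 per arm. The t-test calculation gives 22.02, rounded up to 23. Allowing for 20% loss, 23/0.8 = 28.75, so 29 per arm and 58 in total. The stated figures reproduce, and nothing below changes them. No calculation is given for biochemical failure-free survival.

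**What each endpoint does with a man salvaged before Phoenix failure:**

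| Endpoint | Salvage ADT | Salvage surgery or radiotherapy |
|---|---|---|
| Biochemical failure-free survival | Not an event | Not an event |
| ADT-free survival | Event | Not an event |
| Local, regional and metastasis endpoints | Not named | Not named; seen only if such a failure is also recorded |

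**Inputs for an illustration.** There are 29 men per arm (Study design). The 5-year biochemical failure-free rates of 84% and 77% come from a cohort study cited in the Background and are used only to set a scale. The share of failures salvaged before Phoenix failure, s, is not in the documents; 10% to 30% is assumed. Further assumptions are complete 5-year follow-up, equal true failure in both arms, exponential times for the hazard ratio, and no later Phoenix failure or death among the uncounted men. The last of these makes the results an upper limit for a given s.

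**Expected events.** 58 × (1 − 0.84) = 9.3, or 29 × 0.16 = 4.6 per arm. At 77%: 58 × 0.23 = 13.3, or 29 × 0.23 = 6.7 per arm.

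**Effect of one man.** 1/29 = 3.4 percentage points on his arm's rate. For two men in one arm, 2/29 = 6.9 points, similar in size to the 84% versus 77% contrast in the Background.

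**Equal early salvage in both arms.** With true failure proportion p, the reported rate is 1 − p(1 − s).

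- p = 0.16: s = 10% gives 1 − 0.144 = 85.6%; s = 30% gives 1 − 0.112 = 88.8%. The true rate is 84%.
- p = 0.23: s = 10% gives 1 − 0.207 = 79.3%; s = 30% gives 1 − 0.161 = 83.9%. The true rate is 77%.

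The overstatement is about 2 to 7 points, and the hazard ratio stays at 1.00.

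**Unequal early salvage.** The apparent hazard ratio is ln(1 − p(1 − s₂)) / ln(1 − p(1 − s₁)), with a true value of 1.

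- s₁ = 10%, s₂ = 30%: for p = 0.16, ln(0.888)/ln(0.856) = 0.76; for p = 0.23, ln(0.839)/ln(0.793) = 0.76.
- s₁ = 0%, s₂ = 30%: for p = 0.16, ln(0.888)/ln(0.840) = 0.68; for p = 0.23, ln(0.839)/ln(0.770) = 0.67.

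Swapping the arms inverts these ratios, so the direction is open. For 30% early salvage the loss is 4.6 − 3.2 = 1.4 or 6.7 − 4.7 = 2.0 events in the affected arm.

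**Weight of the comparison.** By Schoenfeld's formula, 66 events are needed for 80% power at a hazard ratio of 0.5. With 9.3 to 13.3 events the power is about 18% to 24%. The estimated rates will therefore carry more weight with readers than the test.

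**The case against.** The strongest reply is that a one-line definition in a condensed article does not show that no handling rule exists. Rules for intercurrent treatment and censoring commonly sit in the full protocol or analysis plan, and the article does not spell out how the Phoenix definition treats salvage. That limits certainty about what will finally be done. It does not dispose of the point, because the article gives an event list and applying it as stated leaves early salvage uncounted.

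Several other objections stand and set the limits of the point:

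- It is tempting to infer that such a man stays failure-free for good. The documents do not support that. PSA is scheduled to 60 months with no indication that it stops at salvage, and a later Phoenix failure or death still counts.
- It is also tempting to infer that the definition favours the 5-fraction arm. Open-label discretion makes differential timing possible, but nothing in the documents shows that it happens or in which direction.
- ADT-free survival shows early salvage ADT, and the local, regional and metastasis endpoints may show other relapses. A reader who sets them beside the biochemical endpoint sees part of the problem. They do not correct the biochemical failure-free figure.
- Counting salvage as an event brings a discretionary act into an endpoint otherwise defined by PSA and death. If salvage came sooner in one arm, that arm would then look worse instead of better. A purely PSA-based definition is defensible for this reason, which is why both versions should be reported.

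**Conclusion.** The point holds in a limited form. As written, the endpoint carries a man salvaged before Phoenix failure as failure-free until a later Phoenix failure or death. That can delay or mask failures and overstate the absolute rate in either arm. The existence of this effect follows from the definition and the discretionary salvage. Its size does not follow from the documents.

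Under the assumptions shown, each such man adds about 3.4 points to his arm's rate, and 10% to 30% early salvage in both arms overstates the rate by about 2 to 7 points. A distorted comparison between arms requires unequal salvage timing, which is an assumption and not something the documents establish.

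This is one of many secondary endpoints in a phase II trial sized only for EPIC bowel function. The primary conclusion and the sample size are untouched. The change is still worth making before outcomes are known.

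**What to change.** Under Secondary endpoints, define the biochemical failure-free survival event as the first of Phoenix failure, start of any salvage treatment for prostate cancer (ADT, surgery or radiotherapy) recorded in the case report form, or death from any cause. Make clear that ADT planned as part of initial treatment is not salvage. Report the version that counts only Phoenix failure or death alongside, as a sensitivity analysis. Give the number of men per arm who were salvaged before Phoenix failure, so that readers can see how far the two versions differ and why.

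The cost is a short change to the definition and one extra analysis. Additional treatment is already captured in the case report form; it should be confirmed that the start date is recorded. The reported failure-free rate may be slightly less favourable, and the revised endpoint is itself open to open-label influence, which the paired analysis makes visible. The change concerns only how outcomes are counted. It sets no rule on when salvage should be given.

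### The secondary endpoint named prostate cancer-free survival counts only prostate cancer deaths, so it is misnamed; it and the two freedom-from-failure endpoints are better reported as cumulative incidence (minor)

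*Protocol article*

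**What the plan says.** The protocol article, under Secondary endpoints, defines the endpoint as "Prostate cancer-free survival: Time from randomization to death attributed to prostate cancer, or last follow-up, whichever occurs first". No form of relapse is an event, and neither is death from another cause.

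Two neighbours in the same list are built differently: "Biochemical failure-free survival: Time from randomization to biochemical failure (based on the Phoenix definition), death from any cause, or last follow-up, whichever occurs first" and "Metastasis-free survival: Time from randomization to development of metastasis, death from any cause, or last follow-up, whichever occurs first". ADT-free survival follows the same pattern, with the start of salvage ADT as its named event. Freedom from local failure and freedom from regional failure count only the first such failure and do not list death.

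The Methods paragraph of the abstract names the endpoint without defining it, in a list ending "metastasis- and prostate cancer-free survival of the hypofractionated arm compared to the conventionally fractionated arm".

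The Analysis plan covers all of these in one sentence: "Time-to-event end points (e.g. overall survival) will be compared between treatment arms using Kaplan-Meier estimates and the log-rank test". It names no competing-risk method. Table 2 schedules "Survival and disease status" from 6 to 60 months after WPRT.

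**The concern.** There are two separate problems.

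The first is the name. By the pattern of its neighbours, prostate cancer-free survival should mean being alive without prostate cancer. As defined, it means not having died of prostate cancer. A man living with metastases is a success under it. Someone who reads only the abstract, where the term stands beside biochemical failure-free and metastasis-free survival, would take it as a measure of disease control. The article says the trial will give an initial understanding of cancer control and that the hypofractionated regimen could become standard if well tolerated and effective, so a figure under this name could be given more weight than it deserves.

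The second is the estimator. Where other-cause death is not an event, it ends follow-up. Kaplan-Meier then treats that man as if he could still have the event later. One minus Kaplan-Meier describes a population in which nobody dies of anything else, and it exceeds the proportion of men who actually have the event.

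**Working it through.** **Name against definition.** The -free survival endpoints compare as follows.

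| Endpoint | Named condition is an event? | Death from any cause is an event? |
|---|---|---|
| Biochemical failure-free survival | yes | yes |
| ADT-free survival | yes (start of salvage ADT) | yes |
| Metastasis-free survival | yes | yes |
| Prostate cancer-free survival | no (only death attributed to prostate cancer) | no |

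The last row is the only one that breaks the pattern, and it does so in both columns.

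**How many men the name could affect.** The Background cites 5-year biochemical failure-free survival of 84% with WPRT plus HDR-BT and 77% with prostate-only radiotherapy plus HDR-BT, in high-risk men. Applied to the planned 58:

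- 58 × (1 − 0.84) = 9.3 men
- 58 × (1 − 0.77) = 13.3 men

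Both trial arms receive WPRT, so the first figure is the closer one. It is illustrative only. The cited cohort's definition of failure is not shown and may include deaths, and this trial also enrols unfavourable intermediate-risk men. On that footing, about 9 is a ceiling on relapses. Every relapsed man still alive would count as prostate cancer-free.

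**Size of the estimator effect.** The plan gives no figure for this endpoint to reproduce; its sample size concerns only the EPIC bowel function endpoint. It also gives no death rates, so the rates here are assumptions. Let F be the 5-year probability that Kaplan-Meier would report as one minus survival, and G the corresponding probability for other-cause death. Assume constant, independent hazards over 5 years:

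- h1 = −ln(1 − F)/5 and h2 = −ln(1 − G)/5
- cumulative incidence = h1/(h1 + h2) × [1 − exp(−5(h1 + h2))]

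Worked example with F = 10% and G = 10%: h1 = h2 = 0.02107, so cumulative incidence = 0.5 × (1 − 0.90 × 0.90) = 0.5 × 0.19 = 9.5%.

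Cumulative incidence over the assumed range:

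| F (1 − KM) | G = 5% | G = 10% | G = 15% | G = 20% |
|---|---|---|---|---|
| 2% | 1.95% | 1.90% | 1.85% | 1.79% |
| 5% | 4.88% | 4.75% | 4.62% | 4.49% |
| 10% | 9.75% | 9.50% | 9.24% | 8.98% |

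The excess runs from 0.05 points (2% against 1.95%) to 1.02 points (10% against 8.98%). In relative terms it is about 2.5% to 11.5%. The largest gap is 58 × 0.0102 = 0.6 of one man. If local or regional failure were as frequent as 16%, the gap would be 0.39 to 1.61 points, and 58 × 0.0161 = 0.93 is still less than one man.

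**Against sampling error.** With 29 men per arm, one man is 1/29 = 3.4 points, and the standard error of a 10% proportion is √(0.10 × 0.90/29) = 5.6 points. The estimator effect is small beside both.

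**The case against.** The case for leaving the text alone has five parts.

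- **The definition sits beside the name, so no analyst can code the endpoint wrongly.** True for the endpoint list. It does not help a reader of the abstract, where the name stands alone.
- **Relapse is not hidden.** This stands. A reader might infer that relapsed men disappear from the results. They do not: local failure, regional failure, biochemical failure, salvage ADT and metastasis each have their own endpoint.
- **The estimator effect is negligible.** Its size is, as shown above. A reader might infer that failure rates will be seriously overstated; nothing in the documents supports that at 58 men and 5 years. The direction of the effect is certain once other-cause deaths occur, and correcting it is nearly free.
- **The log-rank test is not wrong.** This stands. With other-cause deaths censored, it compares cause-specific hazards. Replacing it with Gray's test would answer a different question and is not required.
- **Handling of competing deaths belongs in an analysis plan that is not shown.** Partly right. The article never uses the word censored and never says that one minus Kaplan-Meier will be reported; both are inferred from the definitions and the single named method. That keeps the estimator point secondary. It does not touch the name, because no other document can make the published name fit the published definition.

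Two further inferences go beyond the documents. One is that the reported figure would be near 100%: no prostate cancer death rate is given. The other is that the registry entry carries the same name: that record is not available here.

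**Conclusion.** The endpoint is misnamed. This follows from the text alone and needs no assumption. What is defined is prostate cancer-specific survival, and the name departs from the convention of its neighbours in a direction that flatters disease control.

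The estimator point also holds, for this endpoint and for freedom from local and regional failure, but it is small: about 0.05 to 1.0 percentage points at 5 years, assuming constant independent hazards, 2% to 10% for the event and 5% to 20% for other-cause death. Kaplan-Meier remains right for biochemical failure-free, ADT-free, metastasis-free and overall survival, which all count death from any cause.

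Severity is minor. This is one of many secondary endpoints. The EPIC bowel function primary endpoint, its 5-point margin and the sample size of 58 do not depend on it.

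**What to change.** 1. Rename the endpoint prostate cancer-specific survival in the endpoint list and the abstract, and wherever else the same name proves to be used. If cancer-free survival is really meant, add relapse and death from any cause as events. That version would overlap heavily with biochemical failure-free survival, so renaming is the simpler choice.
2. State how deaths from other causes are handled for this endpoint and for freedom from local and regional failure.
3. For these three, report cumulative incidence by arm (Aalen-Johansen), with other-cause death as the competing event, in place of Kaplan-Meier. The log-rank test may stay, described as a comparison of cause-specific hazards.

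The cost is a few lines of wording and a standard routine at analysis. Cause of death is already needed for the present definition, and survival and disease status are already scheduled, so no visits, patients or extra data are required.
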